**Methods:**

This exploratory, case–control study will recruit patients with heatstroke, patients with sepsis, patients undergoing cardiopulmonary bypass as well as healthy controls at West China Hospital of Sichuan University from 1 January 2023 to 31 October 2023. The four cohorts will be profiled at one time point in terms of lymphocytes, monocytes, natural killer cells, and granulocytes using flow cytometry, and cell populations will be visualized in two dimensions using t-SNE and UMAP, then clustered using PhenoGraph and FlowSOM. Gene expression in the specific immune cell populations will also be compared across the four cohorts, as will levels of plasma cytokines using enzyme-linked immunosorbent assays. Outcomes in the cohorts will be monitored during 30-day follow-up.

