## Introduction

1.

Heatstroke, which can be categorized as classic heatstroke (CHS) or exertional heatstroke (EHS) depending on its cause (1), is the most life-threatening form of hyperthermia (>40.5°C), and it involves central nervous system dysfunction and multi-organ failure (2). Even with intensive care, mortality rates of heatstroke patients can be as high as 30–60% (1, 2). The incidence of heatstroke-related deaths has been increasing globally during the past 2 decades, as record-breaking heatwaves have occurred (1). Heatstroke survivors may experience long-term neurological and cardiovascular complications (1, 2).

Hyperthermia can damage proteins, lipids, and nucleic acids, as well as kill cells directly (3, 4), inducing the production of cytokines to protect against tissue injury (5, 6). If thermoregulation fails to maintain core temperature within an appropriate range, inflammatory responses may become excessive and injure tissue, leading to multi-organ failure and death (7–9), akin to systemic inflammatory response syndrome (SIRS) (10–15). In addition, heatstroke can compromise gastrointestinal integrity, allowing endotoxins and pathogens to enter the circulation and trigger endotoxemia (14). However, potentially informative differences in immune profiles among patients with heatstroke, SIRS, or sepsis have not been fully elucidated.

For lack of a specific biomarker (1), heatstroke is diagnosed based on hyperthermia, history of exposure to extreme heat or vigorous exertion, and alterations of the central nervous system (6, 7). Researchers have undertaken genomic, epigenomic, transcriptomic, proteomic, and metabolomic studies in an effort to identify diagnostic biomarkers (16–18), without much success. The rate of false positive diagnosis of heatstroke remains as high as 24% and the rate of false negative diagnosis as high as 64.5%, especially among patients with atypical symptoms (2). To make matters worse, heatstroke can be difficult to differentiate from sepsis, especially when it involves leukocytosis, which can delay cooling treatments that substantially improve prognosis (1).

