#### Inclusion and exclusion criteria

2.1.1.

Participants will be recruited from the International Medical Center and from the Departments of Emergency Medicine and of Anesthesiology at West China Hospital of Sichuan University. Four cohorts of 40 individuals each will be recruited: heatstroke patients, sepsis patients, patients undergoing CPB, and healthy controls. The inclusion and exclusion criteria for each cohort are shown in Table 1. Participant recruitment and data collection will begin on January 1, 2023 and will continue until October 31, 2023.

**Table 1 tab1:** Inclusion and exclusion criteria for subject enrollment.

Subjects	Inclusion criteria	Exclusion criteria
Heatstroke patients	(1) Age ≥ 18 years	(1) Pregnant women.
	(2) History of exposure to extreme environmental heat or vigorous muscle exertion	
	(3) Core body temperature > 40°C or symptoms of central nervous system (CNS) dysfunction, such as coma, delirium, or convulsions	(2) Comorbid with immune system disease within the 6 months prior to admission, including but not limited to acquired immune deficiency syndrome (AIDS), multiple myeloma, rheumatoid arthritis, systemic lupus erythematosus, multiple sclerosis, myasthenia gravis, scleroderma, Crohn’s disease, and ulcerative colitis.
	(4) Written informed consent to participate	
Sepsis patients	(1) Age ≥ 18 years	(3) Comorbid with malignant tumor and hematological diseases.
	(2) Suspected or known infection	
	(3) Sequential organ failure assessment (SOFA) score ≥ 2	
	(4) Written informed consent to participate	(4) History of organ or bone marrow transplantation.
Patients undergoing CPB	(1) Age ≥ 18 years	
	(2) Valve replacement or coronary artery bypass under cardiopulmonary bypass	
	(3) Written informed consent to participate	
Healthy controls	(1) Age ≥ 18 years	(5) History of immunosuppressive therapy, including glucocorticoids, soluble microbial products (SMSs), polyclonal and monoclonal antibodies, antimetabolite and alkylating agents, or radiotherapy within the 6 months prior to admission.
	(2) Body mass index 18–24 kg/m^2^	
	(3) Health examination within the previous 6 months indicated no abnormality	
	(4) Written informed consent to participate	

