#### Participant matching

2.1.2.

Heatstroke patients will be matched 1:1 with sepsis patients, CPB patients and healthy controls using propensity score analysis based on nearest-neighbor matching and a caliper width of 0.2 of the standard deviation of the logit of the propensity score (20). Covariates during matching of heatstroke and sepsis patients will be sex, age, body weight, Sequential Organ Failure Assessment (SOFA) score (21), comorbidities, and treatment history. Covariates during matching of heatstroke and CPB patients will be sex, age, body weight, comorbidities, and treatment history. Covariates during matching of heatstroke patients and healthy controls will be sex, age, and body weight.

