### Endpoints

2.2.

The aims of this case–control study are to identify the diagnostic immune cells biomarker(s) of heatstroke and prognostic immune cells biomarker(s) of heatstroke within 30 days.

For exploring diagnostic biomarker(s) that distinguishes patients with heatstroke from patients with sepsis, patients with aseptic inflammation and healthy individuals, because this trial is a case–control study, no endpoints can be provided.

For exploring prognostic biomarker(s) for patients with heatstroke, the primary endpoint is all-cause mortality within 30 days. The secondary endpoints include incidence of the organ injury events within 30 days, including neurological dysfunction, acute heart failure, acute renal failure, or respiratory failure, which are diagnosed as following:

Neurological dysfunction will include stroke, which will be diagnosed based on symptoms of unconsciousness or focal neurologic deficit and the results of computerized tomography and magnetic resonance imaging; and delirium, which will be diagnosed as described (22).

Acute heart failure will be diagnosed according to symptoms of breathlessness, tiredness, and fatigue; clinical signs; abnormalities of electrocardiogram(ECG) such as atrial fibrillation, Q waves, left ventricle hypertrophy, and a widened QRS complex (23); left ventricular ejection fraction (LVEF) ≤ 40% based on the results of echocardiography (23); and elevated levels of B-type natriuretic peptide (BNP) or NT-proBNP (24).

Acute renal failure will be defined as stage 3 acute kidney injury according to the KDIGO criteria (25): stage3: creatinine level in serum ≥4.0 mg/dL (353.60 μmol/L) or ≥ 3 times baseline within 7 days, or requirement for renal replacement therapy, or urine output <0.3 mL/kg/h for ≥24 h OR anuria for ≥12 h.

Respiratory failure will be defined as pH < 7.35 and PaCO_2_ > 45 mmHg or as PaO_2_/FiO_2_ < 200 based on invasive or non-invasive ventilation or arterial blood gas analysis (26, 27) within 30 days. If patients with concomitant pulmonary diseases prior to admission meet above diagnostic criteria, the patient will not be considered to have lung injury caused by heatstroke and will be excluded.

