### Minimal sample size

2.3.

We did not calculate minimal sample size to achieve a given statistical power because this is an exploratory study (28, 29) and we are unaware of other studies with a similar design and purpose. Recent studies of the protective effects of precooling and curcumin on organ injury among patients with EHS included only 8–12 participants (30, 31). A study that examined immune cell dynamics during EHS was able to obtain statistically significant results using only 11 patients (32). Therefore, to differentiate the immune profiles, we aim to enroll at least 40 subjects in each of the four cohorts.

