### Statistical analysis

2.5.

Statistical analyses will be performed using Prism version 9 (GraphPad, San Diego, CA, United States). All statistical tests will be two-tailed, and results associated with *p* < 0.05 will be considered significant.

Continuous variables will be checked for normal distribution using the Shapiro–Wilk test and D’Agostino-Pearson omnibus normality test. If normally distributed, continuous data will be reported as mean (SD), and inter-cohort differences will be assessed for significance using one-way ANOVA or Student’s *t*-test. If skewed, continuous data will be reported as median (range or interquartile range), and inter-cohort differences and multiple pairwise comparisons will be assessed using a non-parametric Kruskal Wallis test or Mann–Whitney test.

Categorical variables will be reported as the number of cases (percentage). Inter-cohort differences in such variables will be assessed using the Chi-squared test or Fisher’s exact test. Inter-cohort differences in ordinal variables will be assessed using the Kruskal Wallis test or Mann–Whitney test comparisons.

Subgroup analyses will be performed according to the type of heatstroke (CHS or EHS). CHS always results from passive exposure to high ambient temperature, often accompanied by high humidity. EHS, in contrast, occurs in young individuals during vigorous exercise in hot or temperate environments (1).

Student’s *t*-test or Mann–Whitney test will be used to detect correlations between specific immune cell subsets and prognosis of heatstroke patients. The ability of such subsets to predict heatstroke and prognosis of affected individuals will be assessed using receiver operating characteristic curves, based on optimal thresholds obtained by maximizing the Youden index. Sensitivity, specificity, predictive values, and likelihood ratios will be calculated.

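### Predictive values planned for diagnosing heatstroke would reflect the recruitment quotas of a case-control design, not clinical prevalence

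*Protocol article*

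**What the plan says.** The design is case-control. The abstract states: "This exploratory, case–control study will recruit patients with heatstroke, patients with sepsis, patients undergoing cardiopulmonary bypass as well as healthy controls". Section 2.1.1 fixes the sizes ("Four cohorts of 40 individuals each will be recruited"), section 2.3 makes 40 per cohort a minimum ("we aim to enroll at least 40 subjects in each of the four cohorts"), and section 2.1.2 sets the ratio ("Heatstroke patients will be matched 1:1 with sepsis patients, CPB patients and healthy controls using propensity score analysis").

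Section 2.5 assesses by ROC curve, at Youden-optimal thresholds, how well immune cell subsets predict two things: heatstroke itself, and the prognosis of those who have it. The next sentence covers both: "Sensitivity, specificity, predictive values, and likelihood ratios will be calculated". It mentions no external prevalence and no adjustment.

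On the diagnostic aim, section 2.2 says: "because this trial is a case–control study, no endpoints can be provided". The same sentence names the three groups from which heatstroke is to be distinguished: sepsis, aseptic inflammation and healthy people.

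**The concern.** PPV and NPV are probabilities of disease given a test result, so they depend on how common the disease is among those tested. Where people are sampled by disease status, the sample proportion is a design choice and estimates nothing about clinical practice. Sensitivity, specificity and likelihood ratios condition on disease status, so the sampling ratio does not distort them within a given contrast.

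Followed as written, the plan would report a diagnostic PPV that changes with the number of comparators included, even for a marker whose accuracy is fixed. The article's stated aim is to find diagnostic biomarkers, and its Discussion speaks of accurate diagnosis. A high PPV would be read as the chance that a patient with a positive result has heatstroke, which this sample cannot show by itself.

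**Working it through.** The article gives no accuracy target, prevalence or power calculation, so there is no figure of its own to reproduce beyond 4 × 40 = 160 participants.

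**Inputs from the article**
- 40 per cohort, four cohorts (section 2.1.1).
- 1:1 matching of heatstroke to each comparator (section 2.1.2).

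**Heatstroke share set by design**
- One pairwise contrast: 40/80 = 50%.
- All four cohorts: 40/160 = 25%, that is 1:3.

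Enrolment above the minimum, or loss of unmatched people, could shift the counts, but the share would still come from recruitment and matching.

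**Assumed, because the article gives no values**
- Sensitivity (Se) = specificity (Sp) = 0.85, with 0.80 and 0.90 as a range.
- Clinical prevalences of 10% and 5%, with 1% added for the range.

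**Formulae**, with p the heatstroke share:
- PPV = Se·p / [Se·p + (1 − Sp)(1 − p)]
- LR+ = Se / (1 − Sp)

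**Results at Se = Sp = 0.85**
- p = 0.50: 0.425 / (0.425 + 0.075) = 0.850
- p = 0.25: 0.2125 / (0.2125 + 0.1125) = 0.654
- p = 0.10: 0.085 / (0.085 + 0.135) = 0.386
- p = 0.05: 0.0425 / (0.0425 + 0.1425) = 0.230
- LR+ = 0.85 / 0.15 = 5.67 in every row

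The same in counts: 0.85 × 40 = 34 heatstroke patients test positive. Against one comparator cohort there are 0.15 × 40 = 6 false positives, so PPV = 34/40 = 0.85. Against three cohorts, holding specificity at 0.85 in each, there are 0.15 × 120 = 18, so PPV = 34/52 = 0.65. The marker is the same and only the quota differs.

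**Range over assumed accuracy (PPV)**

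| Heatstroke share | Se = Sp = 0.80 (LR+ 4.0) | Se = Sp = 0.90 (LR+ 9.0) |
|---|---|---|
| 50% (1:1) | 0.80 | 0.90 |
| 25% (1:3) | 0.57 | 0.75 |
| 10% (assumed) | 0.31 | 0.50 |
| 5% (assumed) | 0.17 | 0.32 |
| 1% (assumed) | 0.04 | 0.08 |

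NPV moves the other way. At Se = Sp = 0.80 it is 0.80 at 1:1, 0.92 at 1:3 and 0.97 at 10%.

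**Prognosis.** Within the heatstroke cohort, the share who die or have organ injury by 30 days is observed and not set by a quota. The objection does not reach predictive values there.

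**The case against.** The best defence is that the predictive-value sentence serves two aims and is legitimate for one of them. The article does not say that diagnostic PPV will be presented as clinically applicable, and it plans likelihood ratios alongside, so a reader could apply any prevalence. The study is exploratory, and nothing is lost beyond repair, because the values can be dropped or re-expressed at reporting. This bears on how serious the point is. It does not remove it: the sentence covers diagnosis without restriction, and computing predictive values from the sample as planned yields quota-driven figures.

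A reader might also infer four stronger points, which the article does not support:

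- **The diagnostic ROC has no comparator, so easy comparators could be pooled to flatter the AUC.** Section 2.2 names all three groups and section 2.1.2 builds three separate 1:1 contrasts. Pooling is stated nowhere. Whether the curves are pairwise or pooled is detail that a fuller plan may hold.
- **Bypass patients are an irrelevant comparator.** They represent aseptic inflammation, which the Discussion lists among conditions hard to tell apart clinically.
- **The section 2.2 statement on endpoints leaves the diagnostic aim without a measure.** Section 2.2 appears to use the word for follow-up events such as death and organ injury. Section 2.5 already plans ROC curves, sensitivity and specificity, so no analysis is lost. The reason given is still loosely worded, since a case-control sample can estimate those measures.
- **Heatstroke versus sepsis must be the primary contrast.** The Introduction does say that "heatstroke can be difficult to differentiate from sepsis", but the stated aim covers aseptic inflammation as well. Ranking the contrasts in an exploratory study is a preference.

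**Conclusion.** The point holds for predictive values under the diagnostic aim. As written, the plan yields PPV and NPV fixed in part by a recruitment share of 50% or 25%. At an assumed accuracy of 0.85, the PPV of 0.85 from a 1:1 contrast would be 0.39 at 10% prevalence and 0.23 at 5%. Those sizes rest on assumed accuracies and prevalences; the dependence itself holds for any imperfect marker. Sensitivity, specificity and likelihood ratios are unaffected by the sampling ratio within a contrast, and predictive values for 30-day outcomes in the heatstroke cohort are not open to this objection. The section 2.2 remark on endpoints needs only a wording correction.

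**What to change.** In section 2.5, separate the two aims.

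- **Diagnosis:** report sensitivity, specificity and likelihood ratios for heatstroke against each comparator cohort. Delete PPV and NPV computed from the sample, or give them only by Bayes' rule over a stated range of external prevalences, with the source or assumption for that range.
- **Prognosis:** PPV and NPV may stay for 30-day outcomes within the heatstroke cohort.

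In section 2.2, replace the claim that a case-control design allows no diagnostic endpoint with a statement that the diagnostic aim has no follow-up event and is assessed by the ROC-based accuracy measures of section 2.5.

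The cost is a few sentences. Recruitment, assays, data collection and budget do not change.

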## Discussion

3.

This trial aims to be the first systematic, comprehensive comparison of immune cell profiles across three conditions that can be difficult to differentiate clinically: heatstroke, aseptic inflammation such as in patients undergoing CPB (19), and systemic infection such as in sepsis patients. Our study may succeed in identifying specific immune cell signatures useful for accurate diagnosis of heatstroke and for identifying patients at high risk of worse outcomes. Regardless of whether the study achieves this goal, it should provide a comprehensive understanding of the immune profiles in heatstroke, which may help clarify the course of this life-threatening condition and lay the foundations for immunotherapies that might become the first curative treatments for heatstroke.

To reduce the potential bias of clinicodemographic differences among the four cohorts on their immune cell profiles, we will match the groups based on age, sex, and body mass index.

## Ethics statement

The studies involving human participants were reviewed and approved by the Medical Ethics Committee of West China Hospital, Sichuan University. The patients/participants provided their written informed consent to participate in this study.

